#### National Opinion Research Center DSM-IV Screen for Gambling (NODS-PERC)

This is a short version of the original 17-item scale NODS. It was developed based on four of the DSM-4 criteria for gambling disorder: preoccupation, escape, chasing losses and social consequences. It is used as a screening tool for gambling problems and contains four questions regarding difficulties related to gambling. The questions are answered with “yes” or “no”. If at least one question is answered as “yes”, gambling problems may be present [44].

#### Difficulties in Emotion Regulation Scale (DERS-16)

This is a self-rating scale developed to measure the level of difficulties in emotion regulation. Answers are given on a five-point Likert scale ranging from 1) almost never to 5) almost always. The total score ranges from 16–80, where higher scores indicate higher levels of difficulties in emotion regulation. It is built on five subscales: clarity, goals, impulse, strategies and non-acceptance. Test–retest reliability is 0.85, and Cronbach´s alpha is between 0.92 and 0.95 [45, 46].

#### Brunnsviken Brief Quality of Life Scale (BBQ)

The Brunnsviken Brief Quality of Life Scale was developed in Sweden to measure an individual´s subjective quality of life in a clinical setting [35]. The questionnaire is divided into six different life areas such as “view on life”, “creativity” and “friends and friendship”. Each life area is represented by two statements: the first applies to “satisfaction” and the second applies to “importance”. Both statements are answered on a five-step Likert scale, scored visually from 0–4, with 0 representing “do not agree at all” and 4 “agree completely”. The score on the “satisfaction” statement is multiplied with the “importance” statement. Thus, the total possible score is 96, with higher scores indicating higher perceived quality of life, and with a suggested clinical cut-off score at 52.5. The Cronbach´s alpha was 0.76, and the internal validity was shown to be 0.82. The BBQ will be included in the initial measurements (T0), post-treatment (T3) and at the 3-month follow-up (T4).

#### Motives for online gaming questionnaire (MOGQ-14)

The Motives for Online Gaming Questionnaire is a self-report instrument measuring motives for gaming [47]. It covers seven different motivational factors: social, escape, competition, coping, skill development, fantasy and recreation. The questions are answered on a five-point Likert scale ranging from 1 (almost never) to 5 (most of the time). The questionnaire can be used for various types of games and has been validated in a Swedish context [48].

#### Alcohol Use Disorders Identification Test (AUDIT)

The Alcohol Use Disorders Identification Test is a screening tool for alcohol related problems and identifies individuals with harmful use of alcohol [49]. It consists of ten items divided into three areas: alcohol consumption (item 1–3), symptoms of dependence (item 4–6) and negative consequences of alcohol consumption (item 7–10). Items 1–8 have five response alternatives, scored 0 to 4, while items 9 and 10 has three alternatives, scored 0, 2 and 4. The maximum score is 40, with a cut-off score of 6 for women and 8 for men, indicating hazardous or harmful drinking. The Cronbach´s alpha was 0.82, and test–retest reliability was 0.93. This questionnaire will be administered at the initial visit (T0), post-treatment (T3) and at follow-up (T4).

#### Drug Use Disorders Identification Test (DUDIT)

The Drug Use Disorers Identification Test is a screening tool for the use of drugs and events of drug-related consequences [50]. It is an 11-item instrument categorized in the three areas drug use, dependence symptoms and negative consequences of drug use [50]. Items 1 to 9 have five response alternatives scored 0 to 4, and items 10 and 11 has three alternatives scored 0, 2 and 4. It has a total possible score of 44. Clinical cut-offs for problematic use are 1 for women and 3 for men, and the Cronbach´s alpha was 0.80. This questionnaire will be distributed at the initial visit (T0), post-treatment (T3) and follow-up (T4).

#### Physical activity and sedentary behaviour

The level of physical activity and sedentary behavior will be evaluated using three questions developed by the Research Group for Physical activity and Health at the Swedish School of Sport and Health Sciences. These questions are validated against accelerometer, objective tests (submaximal oxygen uptake test, balance test and vertical jump test) and cardiovascular risk factors. One question measures time spent in exercise training (six response alternatives ranging from 0 to more than 120 min per week), while another question measures time spent in everyday physical activity (seven response alternatives ranging from 0 to more than 300 min per week). The last question measures time spent sitting during a day (seven response alternatives ranging from “almost all day” to “never”) [51]. These questions are recommended by the Swedish National Board of Health and Welfare.

#### Demographics and gaming-related questions

Information about education, living situation, occupation, medication, gaming-related somatic symptoms, length and height is obtained, as well as information about gaming habits. The participants are, for example, asked about preferred game genres, main type of platform used for gaming and treatment goals for gaming.

Scales used only at baseline (T0):

#### Adult ADHD Self-Report Scale (ASRS V1.1) Screener

The Adult Self-Report Scale V1.1 Screener is a shorter version of the ASRS V1.1 Symptoms Checklist and is used to identify adult individuals with symptoms of ADHD [52]. It is a six-item instrument, which asks questions about symptoms of ADHD during the last six months based on symptoms described in the DSM-4. The instrument uses a five-point response scale (0–4) representing “never”, “rarely”, “sometimes”, “often” and “very often” with a total score ranging from 0 to 24. A cut-off of 14 or above is suggested as positive for ADHD (0—9: low negative; 10—13: high negative; 14—17: low positive; 18—24: high positive). In a study by Kim et al. (2013) the Cronbach´s alpha was shown to be 0.89 and the test–retest reliability was 0.88 [53]. Although it was developed for an adult population, the ASRS screener has also shown good reliability for use in adolescents [54].

#### Ritvo Autism and Asberger Diagnostic Scale (RAADS-14 Screen)

The Ritvo Autism and Asberger Diagnostic Scale is a self-assessment form screening for autism spectrum syndromes in adults [55]. The scale has three domains: mentalizing deficits, sensory reactivity, and social anxiety. The response alternatives are: 1) true now and when I was young, 2) true only now, 3) true only when I was young, and 4) never true. The maximum score is 42, with a cut-off of 14 indicating symptoms of autism spectrum disorder. The Cronbach´s alpha was above 0.8.

Scale used only during treatment (T2):

#### Negative Effects Questionnaire (NEQ)

The purpose of the NEQ is to measure negative or adverse effects of psychological treatment, as experienced by the patient [56]. It contains 20 statements connected to experiences from the treatment, for example, “I felt more worried” and “Unpleasant memories resurfaced”. The statements are answered by “yes” or “no”. If the answer is yes, the statement is graded on a five-point Likert scale with the response alternatives 0) “not at all”, 1) “slightly”, 2) “moderately”, 3) “very” or 4) “extremely”. The respondent then reports whether the experience was a result of the treatment or other circumstances. The total score ranges from 0 to 80, and can be divided into five factors: symptoms, quality, stigma, dependency and hopelessness. The reliability has been shown to be good, with a Cronbach´s alpha of 0.95 [57].

Clinical interviews used at screening:

#### Semi-structured diagnostic interview for gaming disorder

This clinical interview will be used as a support for diagnosing GD. It is based on the nine criteria for IGD presented in the DSM-V and is a modified version of a semi-structured interview developed by Vadlin et al. [58]. The proposed cut-off for diagnosis is fulfilment of five or more criteria.

#### The Mini- International Neuropsychiatric Interview (MINI-7.0.1)

The Mini International Neuropsychiatric Interview is a structured screening interview for common psychiatric disorders. It has been updated to reflect the changes in the DSM-5 [27, 30]. It includes questions assessing a wide range of psychiatric disorders including mood and anxiety disorders, suicide risk, and use of psychoactive substances. It also includes items assessing ADHD. The Swedish version of this structured clinical interview will be used to assess psychiatric comorbidity in the assessment of exclusion criteria [59]. It has shown excellent inter-rater reliability (all kappa values over 0.75) and good test–retest reliability (61% of kappa values over 0.75) [27].

### Plans to promote participant retention and complete follow-up {18b}

To encourage the participants to complete the follow-ups, they will be rewarded with a gift card after the post-treatment assessment (T4). Reminders will be sent out by SMS before each follow-up. If the participant discontinues participation before end of study for any reason, they will be contacted by telephone. Standardized questions will be asked in order to complete questionnaires equivalent to those in T3 (see Table 2) as well as the reasons for discontinuation (optional).

### Data management {19}

New participants will be registered and coded every week. The collected data will be regularly entered in IBM SPSS (once a month). All digital data will be stored on a safe server only accessible by the involved researchers through personal identification. Data on paper will be stored for at least 25 years. Data quality will be promoted through the automatic scoring of questionnaires. Range checks for data values will also be performed.

### Confidentiality {27}

All information collected on paper will be stored in a safe placed in a locked room, with the key stored in a locker that can only be accessed with a code. The digital questionnaires will be downloaded to a secure server that can only be accessed by personnel involved in the trial. Personal data in the dataset will be coded and it will not be possible to identify individuals. The key code will be stored separately in a password protected digital folder. All data will be anonymized.

### Plans for collection, laboratory evaluation and storage of biological specimens for genetic or molecular analysis in this trial/future use {33}

Not applicable. No biological specimens will be used in this study.

## Statistical methods

### Statistical methods for primary and secondary outcomes {20a}

Descriptive data will be presented by treatment arm and, where applicable, by timepoint. For numeric variables, summary statistics will include the number of available and missing measurements, mean, standard deviation (SD), median and minimum and maximum values. Treatment comparisons for primary, secondary and exploratory endpoints will be conducted using analysis of covariance (ANCOVA), adjusted for baseline values.

The primary efficacy analysis, which assesses the change in IGDS9-SF from baseline to 12 weeks between the CBT and control groups, will be conducted using analysis of covariance, adjusted for baseline values, with missing data handled through multiple imputation using predictive mean matching. The treatment effect will be tested at a significance level of α = 0.05. Results will be reported as the mean difference with 95% confidence intervals.

Secondary efficacy analyses of changes in GDT and GD-TLFB from baseline to 12 weeks between the CBT and control groups will be conducted using the same methodology as the primary efficacy analysis. To control the overall Type I error rate for secondary endpoints, an alpha-splitting testing procedure will be employed. The two secondary endpoints—GD-TLFB weekly hours and changes in GDT scores from baseline to 12 weeks—will initially be tested with an alpha level of 0.025 each. If the first test (i.e., GD-TLFB) demonstrates statistical significance, the entire probability mass will be transferred to the next secondary endpoint (i.e., GDT), which will subsequently be tested at the 0.05 significance level, with results reported as the mean difference and corresponding 95% confidence intervals.

All statistical tests will be two-tailed, with results presented as mean differences and accompanied with corresponding 95% confidence intervals.

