### Objectives {7}

The primary objective of this trial is to examine the effects of a 12-week CBT-intervention on GD-symptoms, compared to a waitlist control. The secondary objective is to study the effects on weekly hours of gaming. The hypothesis is that CBT will lead to a reduction of GD-symptoms and a decrease of weekly hours in gaming, compared to the wait list control.

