#### Gaming Disorder Timeline Follow-Back (GD-TLFB)

This gaming-related diary is the third main outcome measure. It was originally developed to track alcohol-consumption and has been adapted to measure gaming behavior [43]. The adapted version collects measurements on a weekly basis: number of days gaming, total hours of gaming and leisure time without screen (e.g., reading a book, meeting friends, or exercising). The diary will be filled out weekly during treatment to evaluate the process. It will also be used as a visual tool for the participants to gain an overview of their gaming habits. The control group will also fill out the gaming diary during the control period.

Exploratory outcomes are:

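### The secondary tests have their own 5% and do not depend on the primary result, so the joint false-claim rate is roughly 7–10%; a one-sentence gate on the primary would hold it at 5%

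*Protocol article*

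**What the plan says.** All the rules stand in the protocol article, Statistical methods for primary and secondary outcomes {20a}.

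- Primary (IGDS9-SF): "The treatment effect will be tested at a significance level of α = 0.05".
- Sidedness: "All statistical tests will be two-tailed".
- Scope of the multiplicity control: "To control the overall Type I error rate for secondary endpoints, an alpha-splitting testing procedure will be employed".
- Starting levels: GD-TLFB and GDT "will initially be tested with an alpha level of 0.025 each".
- Transfer: "If the first test (i.e., GD-TLFB) demonstrates statistical significance, the entire probability mass will be transferred to the next secondary endpoint", that endpoint being GDT, "which will subsequently be tested at the 0.05 significance level".

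The only trigger in the procedure is the GD-TLFB result. The section does not say what happens to the secondary tests if IGDS9-SF is not significant.

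Two other places bear on how much weight the secondaries carry. Objectives {7} puts symptoms and hours in one hypothesis: "The hypothesis is that CBT will lead to a reduction of GD-symptoms and a decrease of weekly hours in gaming". The description of the diary under data collection says: "This gaming-related diary is the third main outcome measure". On the other hand, Outcomes {12} lists both GD-TLFB and GDT as secondary, and Objectives {7} names gaming hours as the secondary objective.

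**The concern.** The primary uses 0.05 and the secondary pair uses a further 0.05, with no order between the two families. A trial that misses on IGDS9-SF can therefore still report, under its own rules, a multiplicity-controlled significant effect on gaming hours or on GDT.

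This matters more here than for a list of exploratory measures. The secondaries have a formal alpha procedure and sit in a tier above the exploratory outcomes. GDT is a second self-report scale of gaming symptoms, reported to correlate 0.82 with the primary scale. With self-reported outcomes, a waitlist comparator and only the statistician blinded, it helps to fix beforehand which result carries the claim and what a secondary result means if the primary fails.

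**Working it through.** **Inputs from the protocol article.** Primary alpha 0.05, secondary alphas 0.025 and 0.025, transfer GD-TLFB to GDT, two-sided tests (section {20a}). Score correlation IGDS9-SF/GDT of 0.82 (section on the GDT). Sample size inputs: difference 5, SD 10, power 80%, alpha 5%, dropout 20% (Sample size {14}).

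**Assumptions.** The correlation of GD-TLFB with the other two is not given; I take it as equal for both and vary it from 0 to 0.8. The 0.82 is a validation figure for scores, not for baseline-adjusted treatment-effect statistics, so using it for the latter is also an assumption. Each test is taken to hold its nominal level, at one final analysis.

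**1. The plan's own figures.** A two-sample t-test with 5/10 = 0.5 SD gives 63.8, so 64 per arm (power 0.801), 128 in total, and 128/0.8 = 160. This agrees with the protocol and rests on the primary alpha only. Within the secondary family, 0.025 + 0.025 = 0.05 is an upper bound; if independent, 1 − 0.975² = 0.0494. The transfer cannot raise this when both nulls are true, because it operates only after GD-TLFB has already been rejected. If GD-TLFB truly works and GDT does not, the only possible error is on GDT, at no more than 0.05. The secondary family is therefore controlled.

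**2. All three outcomes together, no true effect.** At least one false claim occurs if |Z| > 1.960 for IGDS9-SF, or |Z| > 2.241 for GD-TLFB, or |Z| > 2.241 for GDT.

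- Upper bound: 0.05 + 0.025 + 0.025 = 0.10.
- Independent statistics: 1 − 0.95 × 0.975 × 0.975 = 0.0969.
- Correlated statistics: simulation of the stated rule, 6 million trivariate normal draws per scenario.

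With 0.82 between IGDS9-SF and GDT:

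| GD-TLFB correlation with both | Any false claim | Secondary family alone | Secondary claim, primary not significant (any − 0.05) |
|---|---|---|---|
| 0 | 0.0835 | 0.0493 | 0.0335 |
| 0.2 | 0.0828 | 0.0488 | 0.0328 |
| 0.4 | 0.0804 | 0.0476 | 0.0304 |
| 0.5 | 0.0785 | 0.0464 | 0.0285 |
| 0.6 | 0.0761 | 0.0449 | 0.0261 |
| 0.8 | 0.0689 | 0.0401 | 0.0189 |

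Other values: with 0.6 between IGDS9-SF and GDT, and GD-TLFB from 0 to 0.6, the any-claim rate runs from 0.0905 to 0.0821. With all correlations 0.5 it is 0.0867. The lowest value on the whole grid (0.9 and 0.8) is 0.0657. The last column reaches 0.0969 − 0.05 = 0.0469 under independence.

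**3. A true effect on hours only.** If GD-TLFB is almost certain to be significant and the other two are null, GDT is tested at 0.05 beside the primary at 0.05. The false-claim rate is 1 − 0.95² = 0.0975 if independent and 0.0766 at 0.82.

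**4. With a gate on the primary.** If the primary null is true, any false claim requires rejecting it, so the rate is at most 0.05. If the primary effect is real, errors can arise only in the secondary family, which step 1 bounds at 0.05. The joint rate is thus at most 0.05 for any correlation.

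**The case against.** The strongest defence is that the plan does what it says. It limits its multiplicity control to the secondary endpoints, names one primary with its own 0.05, and keeps both promises. Separate control of the two families is a coherent choice, and control across both is a stricter standard. That stands, and it rules out three stronger readings.

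- A reader might infer that the plan promises 5% over all three outcomes and breaks that promise. No section makes the promise, and the primary test is not inflated.
- A reader might fix the joint rate at 8–9%. The document does not support so narrow a range. Its one reported correlation gives 6.9–8.4%; values near 9% need a weaker IGDS9-SF/GDT correlation.
- A reader might treat the three measures as co-primary because the diary is called a main outcome. That phrase falls in the list of secondary outcomes; the trial design, outcomes and sample size sections all rest on GD symptoms measured by IGDS9-SF.

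It is also fair that 5 points of the joint rate are the primary's ordinary error, which no gate removes. The part at issue is the remaining 2–5 points.

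One may add that an analysis plan not shown could contain the gate. If it does, the point is settled by carrying it into the protocol. But the article does not merely leave this open: it sets out levels, order, transfer and final level, and an analyst following it would test the secondaries whatever the primary shows.

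**Conclusion.** The point holds as a cheap improvement, not as an error in the plan. The stated procedure permits a formally significant secondary claim after a failed primary, because nothing connects the two families. With no true effect, that happens in about 2–5% of trials, and at least one false efficacy claim occurs in roughly 7–10%. The range reflects unreported correlations. The rate exceeded 5% in every scenario examined. The primary analysis, its error rate, the sample size and the control within the secondary family are all sound and unaffected.

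**What to change.** Add one sentence to section {20a}: GD-TLFB and GDT are tested confirmatorily, with the existing split and transfer, only if the IGDS9-SF test is significant at two-sided 0.05; otherwise both are reported with estimates and 95% confidence intervals and labelled descriptive. Settle this before any outcome data by arm are seen.

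The sample size stays at 64 per arm and 160 recruited, since the primary alpha does not change. The secondary levels are also the same as now whenever the primary succeeds. The cost is that a failed primary rules out any confirmatory secondary claim. At the planned 80% power this would happen in about 1 − 0.80 = 20% of trials even if the assumed 5-point effect on IGDS9-SF is real. If the investigators prefer to keep the families separate, the protocol should say so and state that the 5% level does not extend across primary and secondary outcomes together.

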### Interim analyses {21b}

We plan to conduct interim analyses when approximately 50% of the planned total sample has finished the trial period [60]. These analyses will be made to investigate the actual standard deviation in the study sample (as previous knowledge about this is extremely limited), to make a more informed decision about sample size. The interim analyses also enable decisions about implementation in regular care as fast as possible, as treatment options for this group of patients are lacking. Based on the data at that point of time sample size will be adjusted. These decisions will be made by the trial steering committee in collaboration with the assigned statistician.

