### Composition of the data monitoring committee, its role and reporting structure {21a}

N/a. The present study is judged as a low-risk trial, not involving any medications or medical equipment.

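### The half-way interim is also meant to inform implementation decisions, yet the primary test keeps the full two-sided 0.05, so the 5% type I error is not protected

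*Protocol article*

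**What the plan says.** All references are to the protocol article.

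- **Interim analyses {21b}, timing:** "We plan to conduct interim analyses when approximately 50% of the planned total sample has finished the trial period".
- **Same section, first purpose:** "These analyses will be made to investigate the actual standard deviation in the study sample", so that the sample size can be reconsidered.
- **Same section, second purpose:** "The interim analyses also enable decisions about implementation in regular care as fast as possible, as treatment options for this group of patients are lacking".
- **Same section, consequence:** "Based on the data at that point of time sample size will be adjusted". The trial steering committee decides, together with the statistician.
- **Statistical methods {20a}, primary outcome:** "The treatment effect will be tested at a significance level of α = 0.05". The section also says "All statistical tests will be two-tailed". Its multiplicity procedure covers only the two secondary endpoints, and it does not mention the interim.
- **Data monitoring committee {21a}:** there is none, because "The present study is judged as a low-risk trial, not involving any medications or medical equipment".
- **Blinding {17a}:** treating staff and research personnel are unblinded. The statistician receives a coded file.

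**The concern.** A pooled SD says nothing about whether the treatment should enter regular care. A decision on that needs the difference between the arms, so the second purpose implies an efficacy look at about half the information. The protocol then tests the primary outcome at the full 0.05, as if no one had looked.

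The sentence on adjusting the sample size refers to the data in general. If the observed effect entered that decision, the ordinary final test would no longer have its nominal level.

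What is at stake is the error rate of the primary claim. Conduct also matters. Participants know whether they are on the waitlist, the outcome is self-reported, and no independent body holds the interim results. The coded file does not settle this. Coded groups can still be compared, and an implementation decision requires knowing which group is which.

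**Working it through.** **1. The plan's own figure.** Sample size {14} gives a difference of 5 points, SD 10, 80% power, two-sided 5% and a t-test. Noncentral-t power is 0.795 at 63 per arm and 0.801 at 64, so 64 per arm (128 in total) reproduces. With 20% drop-out, 128/0.8 = 160, which also reproduces. This is a single-look calculation, and no interim enters it.

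**2. An efficacy look followed by a final test at 0.05.** Inputs are an information fraction of 0.5 ({21b}) and a final two-sided level of 0.05 ({20a}). The interim level is an assumption, because none is stated. Under the null, the interim and final statistics Z1 and Z2 are bivariate normal with correlation √0.5 = 0.707. The overall error is 1 − P(|Z1| < c1, |Z2| < 1.96), where c1 is the critical value for the assumed interim level.

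| Assumed interim level | Overall type I error |
|---|---|
| 0.05 | 8.3% |
| 0.025 | 6.4% |
| 0.01 | 5.5% |
| 0.005 | 5.2% |
| 0.001 | 5.02% |

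With the interim read at 0.05, the result is 8.6% at an information fraction of 0.4 and 8.0% at 0.6.

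**3. Sample-size change followed by an ordinary final t-test at 0.05.** This was simulated under the null with 400,000 runs and 32 or 40 per arm at the interim. Here no claim is made at the interim unless stated.

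- Driven only by the within-group SD: about 5.1% to 5.2%.
- Driven by the interim effect, with a cap of 80 to 1,000 per arm: about 6.0% to 8.0%.
- Theoretical worst case: for each Z1, the second-stage size is chosen to maximise the conditional chance of rejection, and a positive result may also be claimed at the interim if |Z1| ≥ 1.96. With r the ratio of second-stage to interim size, that chance is Φ((Z1 − 1.96√(1+r))/√r) plus the matching lower-tail term. Averaged over Z1, this gives 10.3% if r is at most 5 and 11.2% with no cap.

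**4. What would hold 5% with one look at half the information.** For O'Brien-Fleming the constant is 1.977. The critical values are 1.977 × √2 = 2.796 at the interim (p = 0.0052) and 1.977 at the end (p = 0.0480), and the overall error is 0.050. Alternatives are Pocock at 0.0294 for each look, Lan-DeMets O'Brien-Fleming-type spending at 0.0031 and 0.0490, and Haybittle-Peto at 0.001 and 0.0498.

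**The case against.** The protocol describes no interim hypothesis test, no threshold and no early stopping. A look that leads to no claim, no stopping and no effect-driven change of sample size leaves the final test at 5%. Implementation can be read as a service decision rather than a rejection of the null. The named driver of the sample-size change is the SD. Boundaries, formulas and limits are commonly left to an analysis plan, and that plan is not shown. Having no monitoring committee is a reasoned choice, and Composition {5d} separates the steering committee from the trial management group.

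Most of this stands, and it rules out three stronger readings that a reader might infer.

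- **That the 5% level has definitely been lost, at 8.3% or more.** The text does not show this, because 8.3% depends on an assumed interim level of 0.05.
- **That the sample-size change is unrestricted.** No limit is stated, but in context the SD is the likely driver, and it adds almost nothing.
- **That the trial could shrink below those already studied.** At SD 7 the requirement is 64 evaluable, against 80 finishing at the interim (half of 160). But 64/0.8 = 80 recruited, so if the 80 include drop-outs the requirement is just met.

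Nor do the documents show that treating staff would learn interim results, although nothing states that they would not.

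The objection does not remove the core. The protocol itself fixes the implementation use of the interim, the data-based adjustment, who decides and the final 0.05. An analysis plan that added any of the boundaries in step 4 would need a final level below the one printed in {20a}.

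**Conclusion.** The point holds in a limited form and should be fixed. The interim has a purpose that implies a between-arm look, the sample-size sentence is not confined to a blinded SD, and the primary test makes no allowance for either. The stated 5% is therefore unprotected; it is not shown to be broken.

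The size depends on the unwritten rule. It is negligible if only the SD is used or if the interim threshold is very strict. It reaches 8.3% if the effect is acted on as positive at p<0.05. The 10% to 11% figure is a theoretical limit that requires both a sample size chosen freely after seeing the effect and a possible positive claim at the interim. All two-look figures assume one look at about half the information. The planned sample size reproduces and is not in question.

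**What to change.** **Preferred.** State in Interim analyses {21b} that the interim is limited to a blinded re-estimation of the pooled SD, without arm labels and with no between-arm comparison computed or released. Give the adjustment rule and its limits in advance; keeping 160 as a minimum with a stated maximum is one option. Remove the implementation sentence. The final test can then stay at 0.05. The cost is wording only, and implementation decisions wait for the final analysis.

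**If an efficacy look is wanted.** Pre-specify an alpha-spending boundary, for example two-look O'Brien-Fleming with about 0.005 at the interim and 0.048 at the end. Change the level in Statistical methods {20a} to match, and restrict interim results to someone not involved in running the trial. The cost is a slightly lower final level and arranging that person.

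Either change must be made before interim data are seen, because a rule written afterwards cannot restore the error rate.
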